### Trial design

2.1

This clinical trial is a randomized, multi-centre, open-label study that aims to compare the safety and efficacy between afatinib monotherapy and combination therapy with afatinib plus HAD-B1 for the treatment of patients with locally advanced or metastatic EGFR-mutation-positive NSCLC. Participants will be randomized using a ratio of 1:1 into a treatment group (afatinib 20–40 mg/day plus HAD-B1 2 tablets [972 mg/day]) and a control group (afatinib 20–40 mg/day monotherapy) and will be treated for 16 weeks. As treatment continues, follow-up visits will be scheduled at Day 1, week 2, 4, 8, and 16. Physical examination, vital signs, ECOGPS, clinical laboratory examination, tumor marker examination, imaging diagnosis and tumor evaluation, health-related quality of life survey, combined drug confirmation, and abnormal case evaluation are all performed during each visit. Furthermore, for cold-heat pattern identification and genetic search studies, PMRA chip tests and cold-heat pattern identification surveys are performed prior to randomization.

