### Outcome measures

2.6

**The primary measurement** is comparison of starting dose maintenance rate for afatinib and disease adjustment rate (DCR) at 16 weeks in accordance with RECIST 1.1 of Afatinib + HAD-B1 combined group and afatinib monotherapy group. The secondary outcomes are comparisons of the Progressive Free Survival (PFS) determined by RESIST 1.1, overall survival rate (OS), objective response rate (ORR), tumor size reduction, time to progression (TTP), HRQoL, and tumor markers (CEA, NSE) between the 2 groups. The PFS, ORR, DCR, and TTP are evaluated on the basis of RECIST 1.1 criteria.^[10]^ This clinical trial will explore whether the prognosis varies according to cold-heat pattern in Korean medicine. Cold-heat pattern identification will be evaluated using the usual symptom-based CHPIQ, which has been recognized for its reliability and validity.^[13]^

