#### Analysis of second outcome variables

2.10.2

We will compare and evaluate the following between the treatment group and the control group at each time point from the baseline (0 week) to 16 weeks: Progressive survival period (PFS), the time to progression (TTP), and the overall survival rate (OS) present descriptive statistics (number of subjects tested, mean, standard deviation, median, minimum and maximum) and compare statistical significance through Kaplan–Meier analysis. The frequency and percentage of changes in objective response rates (ORR), QOL (EORTC QLQ-C30, EORTC QLQ-LC13, EQ-5D) according to RECIST 1.1 will be presented, and the statistical significance of differences between groups will be analyzed using Chi-square test or Fisher’s exact test.

The reduction of tumor size and tumor markers present descriptive statistics by dose group (number of subjects, mean, standard deviation, median, minimum, and maximum), and statistical significance of differences between groups is to be analyzed by two-sample-test or Wilcoxon signified rank test.

The statistical significance of the variation within each group is tested as either a paired *t*-test or a Wilcoxon signed rank test.

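### Quality-of-life scores are merged with ORR under RECIST 1.1 and compared between arms only as frequencies by chi-square or Fisher, with no baseline adjustment in that test

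*Protocol article*

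**What the plan says.** Section 2.6 of the protocol article (Outcome measures) lists HRQoL among the secondary between-group comparisons: "tumor size reduction, time to progression (TTP), HRQoL, and tumor markers (CEA, NSE) between the 2 groups". Section 2.1 (Trial design) states "follow-up visits will be scheduled at Day 1, week 2, 4, 8, and 16" and adds that "health-related quality of life survey, combined drug confirmation, and abnormal case evaluation are all performed during each visit". Repeated scores, including a baseline, should therefore be available.

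Section 2.10.2 (Analysis of second outcome variables) opens by framing the secondary comparisons "at each time point from the baseline (0 week) to 16 weeks". It then handles ORR and quality of life in one sentence, whose first half reads "The frequency and percentage of changes in objective response rates (ORR), QOL (EORTC QLQ-C30, EORTC QLQ-LC13, EQ-5D) according to RECIST 1.1 will be presented". For the comparison of the two arms on these outcomes, its second half prescribes a single kind of test: "the statistical significance of differences between groups will be analyzed using Chi-square test or Fisher’s exact test".

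The next sentence treats other numeric outcomes differently. It begins "The reduction of tumor size and tumor markers present descriptive statistics by dose group (number of subjects, mean, standard deviation, median, minimum, and maximum" and goes on to a two-sample comparison. The section closes with a general sentence that names no outcome: "The statistical significance of the variation within each group is tested as either a paired *t*-test or a Wilcoxon signed rank test".

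**The concern.** There are two problems in the one sentence.

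- **The criterion does not fit.** RECIST 1.1 is a tumour-response standard, and sections 2.3 and 2.6 of the article use it that way. It cannot say whether a QLQ-C30, QLQ-LC13 or EQ-5D score has changed. The sentence gives no other category for these scores, so for quality of life it cannot be carried out as written.
- **The test does not fit the data.** Numeric scores must be cut into categories before a chi-square or Fisher test can be applied. That discards information, and the result then depends on where the cuts fall. In an open-label trial it is better that no such choice remains open once results are visible.

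What is at stake is the precision and interpretability of a named secondary outcome. The printed method yields a p-value on category counts, not a difference in scores with a confidence interval.

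**Working it through.** **The plan's own figure.** Section 2.9 gives 64 per group for dose maintenance of 57.6% against 80.0%. Assuming two-sided 5% and 80% power (neither is stated there), the unpooled formula gives

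n = (1.960 + 0.842)² × (0.576×0.424 + 0.80×0.20) / 0.224² = 7.849 × 0.4042 / 0.0502 = 63.2, so 64.

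The figure reproduces. It belongs to the primary outcome; the article gives no effect, SD, correlation or cut-point for quality of life. The rest is therefore illustrative.

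**Assumptions.** 64 per arm, two-sided 5%, normally distributed change scores, and a true difference of d standard deviations of change, with d = 0.3, 0.5 and 0.8.

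**Step 1: t test on change.** The noncentrality is d × √(64/2) = 5.657 d, with 126 degrees of freedom.

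**Step 2: two categories, cut midway between the arm means.** The proportions above the cut are Φ(−d/2) and Φ(d/2). Power of the uncorrected chi-square test is summed exactly over all pairs of binomial counts.

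| d | Proportions above cut | Chi-square power | t-test power |
|---|---|---|---|
| 0.3 | 44.0% v 56.0% | 26% | 39% |
| 0.5 | 40.1% v 59.9% | 59% | 80% |
| 0.8 | 34.5% v 65.5% | 94% | 99% |

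**Step 3: other cuts at d = 0.5.** A cut 0.5 SD above the control mean gives 30.9% v 50.0% and power 61%. A cut 1.0 SD above gives 15.9% v 30.9% and power 52%. Fisher's exact test, the alternative the article names, has 53% at the mid-point cut.

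**Step 4: the large-sample loss.** Relative to comparing the normal score itself, a split at the centre has efficiency φ(0)²/(0.5×0.5) = 0.159/0.25 = 0.64. About 36% of the information is lost.

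**Step 5: baseline as covariate.** With baseline-to-follow-up correlation r, the SD of change is σ√(2(1−r)) and the ANCOVA residual SD is σ√(1−r²). The standardised effect rises by the ratio √(2/(1+r)).

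- r = 0.5: ratio 1.155, effect 0.5 × 1.155 = 0.577, power 90%.
- r = 0.7: ratio 1.085, effect 0.5 × 1.085 = 0.542, power 86%.

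**The case against.** **It is a condensed article and the sentence may be a drafting slip.** Responder definitions often sit in a full protocol or analysis plan, and quality of life may simply have been run together with ORR. That explains the missing category. It does not remove the point: a method is printed, and it is unsuitable. A later plan that follows it inherits the problem, and one that departs from it contradicts the published protocol.

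**A reader might infer that baseline is not used at all.** The document does not support that. The sentence speaks of changes, the section frames comparisons from week 0, and the closing sentence on paired tests can be read as covering quality of life. What is absent is baseline adjustment in the between-group test; a within-group paired test does not compare the arms.

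**A reader might also infer that weeks 2, 4 and 8 are thrown away.** That is not supported either, because the section compares groups at each time point. What it lacks is an analysis that uses the visits jointly.

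**The criticism does not carry over to CEA and NSE.** They already have a continuous between-group comparison.

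**The size of the loss depends on the assumed effect.** This stands. The gap is widest near 0.5 SD and narrows to about 5 points at 0.8 SD. With more than two ordered categories the loss would be smaller.

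**Importance is limited.** This also stands. Tolerability is addressed directly by the primary dose-maintenance rate and by the safety assessments in section 2.7, and quality of life is one of several secondary outcomes.

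**Conclusion.** The point holds in this form: the only between-group method printed for the three quality-of-life instruments is a categorical test, tied to a criterion that cannot classify them, without baseline adjustment in that test or joint use of the repeated visits. The contrast with tumour size and tumour markers in the next sentence shows that the article elsewhere gives numeric outcomes a numeric analysis.

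A two-category mid-point split costs roughly 13, 21 and 5 percentage points of power at 0.3, 0.5 and 0.8 SD. At 0.5 SD, ANCOVA would add a further 6 to 10 points over the t test. These figures rest on assumed effects, correlations, cuts and normality; only the 64 per arm comes from the document. The direction of the loss does not depend on the particular effect chosen. The sentence should be corrected, but neither the primary analysis nor the sample size is affected.

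**What to change.** In section 2.10.2, and in the analysis plan to match:

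1. Give quality of life its own sentence, separate from ORR, and remove the reference to RECIST 1.1 for it.
2. Compare each scale score between groups with the baseline score as covariate, by ANCOVA at week 16 or a mixed model over weeks 2, 4, 8 and 16 with arm, visit and arm-by-visit terms. Report the adjusted mean difference with its 95% confidence interval.
3. Keep chi-square or Fisher for ORR, and for any supportive quality-of-life responder proportion whose threshold is fixed in advance.

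A two-sample comparison of change scores would already remove the loss from categorising; the covariate adds precision. The cost is wording and routine programming. No new data are needed and the sample size does not change.

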## Introduction

1

Around 85% of primary lung cancers are non-small cell lung cancer (NSCLC).^[1]^ Numerous oncogenic drivers, including mutations in the genes encoding the epidermal growth factor receptor (EGFR), have been recognized in NSCLC. EGFR mutations are found in 47% of lung adenocarcinomas, the most frequent NSCLC subtype in Asia-Pacific, and in 43% of the adenocarcinomas in the Republic of Korea.^[2]^ The activating mutations in EGFR lead to increased signaling downstream of the receptor, resulting in cellular growth and proliferation and in the promotion of tumor development due to enhanced metastatic spread and resisting apoptotic signals.^[3]^ Platinum-based chemotherapy has been the basis for the treatment of patients with advanced or metastatic NSCLC, but the availability and use of EFGR - tyrosine kinase inhibitors (EGFR TKIs) have significantly changed the management of patients with NSCLC harboring EGFR mutations. Gefitinib, erlotinib, and afatinib are 3 widely used EGFR-TKIs with proven efficacy for the treatment of patients advanced or metastatic NSCLC.^[4]^

In 2013, afatinib was approved by the U.S. FDA for the first line treatment of patients with locally advanced or metastatic NSCLC who harbor nonresistant EGFR mutations.^[5]^ The clinical effectiveness of afatinib in the treatment of such patients has been confirmed by the results of recent real-world studies.^[6]^ Despite the high disease control rates, almost all patients eventually experience acquired resistance-mediated disease progression. Therefore, new combination regimens are needed to delay or overcome this acquired TKI resistance.

HangAmDan-B1 (HAD-B1) is a traditional Korean medicine composed of *Panax ginseng C.A., Panax notoginseng Radix, Cordyceps militaris, and Boswellia carterii BIRDWOOD* (Table 1). Preclinical studies have shown that HAD-B1 has an anti-lung-cancer effect in xenograft animal model experiments using A549 lung cancer cells and A549/CR cells.^[7]^ The results revealed that the activities of caspase-3, -8, and -9 in the HAD-B1-treated group were generally increased in the same way as they were in the afatinib group, suggesting its potential as a novel therapeutic agent for use in afatinib plus HAD-B1 combined therapy for inhibiting acquired resistance. Also, our previous exploratory study to assess the efficacy and safety of HAD-B1 for dose-finding in EGFR-positive NSCLC subjects who need afatinib therapy is currently in progress.^[8]^

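### Secondary comparison of tumour size, CEA and NSE: no baseline adjustment, no stated scale for the reduction, and summaries labelled by dose group in a two-arm trial

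*Protocol article*

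**What the plan says.** Section 2.6 of the protocol article lists tumour size reduction and "tumor markers (CEA, NSE) between the 2 groups" among the secondary outcomes. Section 2.1 schedules "tumor marker examination, imaging diagnosis and tumor evaluation" at the visits.

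Section 2.10.2 gives the analysis. For these outcomes, "The reduction of tumor size and tumor markers present descriptive statistics by dose group (number of subjects, mean, standard deviation, median, minimum, and maximum"; then, "statistical significance of differences between groups is to be analyzed by two-sample-test or Wilcoxon signified rank test". Change within each group is "tested as either a paired *t*-test or a Wilcoxon signed rank test". The section neither says whether the reduction is absolute, percent or logarithmic nor mentions a covariate.

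On grouping, the same section opens with "We will compare and evaluate the following between the treatment group and the control group at each time point". The design in section 2.1 is "Participants will be randomized using a ratio of 1:1 into a treatment group (afatinib 20–40 mg/day plus HAD-B1 2 tablets [972 mg/day", with afatinib alone as control. No dose groups are defined anywhere.

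**The concern.** Three features of the same sentence deserve attention.

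- **Baseline is not used as a covariate.** Baseline markers and tumour measurements are available, and follow-up values normally correlate with them. An unadjusted test of change leaves usable precision behind.
- **The scale is open.** The paired t-test within groups works on follow-up minus baseline, so a programmer could take the reduction as an absolute difference. If the markers are right-skewed, patients with high baselines would then carry much of the variance of the comparison.
- **The grouping label is wrong for this design.** Read literally, the only dose that varies is afatinib (20–40 mg/day, changeable on the investigator's judgment under section 2.5). That is not a randomised grouping, and keeping the starting dose is itself a primary outcome.

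At stake is the precision and clarity of secondary comparisons. Neither the primary outcomes nor the sample size is affected.

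**Working it through.** **1. The plan's own figure.** The only design calculation (section 2.9) is for starting dose maintenance, 57.6% against 80.0%. The article states neither alpha nor power. Assuming two-sided 5% and 80%, the unpooled formula gives (1.960 + 0.842)² × (0.576 × 0.424 + 0.80 × 0.20) / 0.224² = 63.2, rounded up to the stated 64 per group. This says nothing about CEA, NSE or tumour size; only n = 64 per arm is carried forward.

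**2. Assumed inputs.** The article gives no distribution, SD, correlation or effect for these outcomes. Assumed: log-normal marker; treated-to-control ratio 0.60, so the log difference is |ln 0.60| = 0.511; log-SD σ = 1.0 or 1.5, equal at baseline and follow-up; log-scale correlation ρ = 0.6 or 0.8; all 64 per arm measured.

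**3. Gain from baseline adjustment on the log scale.**

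- Variance of log change: 2σ²(1 − ρ). Residual variance after ANCOVA: σ²(1 − ρ²). Their ratio is (1 + ρ)/2, which is 0.80 at ρ = 0.6 and 0.90 at ρ = 0.8.
- Power ≈ Φ(0.511 / (SD × √(2/64)) − 1.96).
- Example, σ = 1.0 and ρ = 0.6. Log change: SD = √0.8 = 0.894, SE = 0.158, Φ(3.23 − 1.96) = 90%. ANCOVA: SD = √0.64 = 0.80, SE = 0.141, Φ(3.61 − 1.96) = 95%.

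| σ | ρ | Log change, unadjusted | Log ANCOVA | Simulated (3000 trials): log change, ANCOVA |
|---|---|---|---|---|
| 1.0 | 0.6 | 90% | 95% | 90%, 95% |
| 1.0 | 0.8 | 99.5% | 99.8% | 99.5%, 99.7% |
| 1.5 | 0.6 | 58% | 67% | 57%, 66% |
| 1.5 | 0.8 | 86% | 89% | 85%, 88% |

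**4. Loss if the reduction is read as absolute change.** Same assumptions, 2000 simulated trials per scenario; ranges run over σ = 1.0–1.5 and ρ = 0.6–0.8.

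| Control-arm decline | t test, absolute change | Rank-sum, absolute change |
|---|---|---|
| None | 16–72% | 41–95% |
| Values halve | 8–23% | 23–52% |

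The t test on log change gives 57–99.6% over the same scenarios.

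**5. Dependence on skew.** A second model takes log change as independent of baseline, with the control arm halving, ratio 0.60, and SD of log change 0.5 or 1.0 (first and second figure in each cell).

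| Baseline log-SD | t test, absolute change | Rank-sum, absolute change | t test, log change |
|---|---|---|---|
| 0.4 | 94%, 56% | 95%, 63% | 100%, 82% |
| 1.0 | 38%, 30% | 66%, 45% | 100%, 81% |
| 2.0 | 8%, 8% | 36%, 37% | 100%, 82% |

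A rank-sum test on the ratio to baseline gave about 79–100% in these rows, so under this model scale matters more than the choice between a t and a rank test. With no treatment effect, rejection was 2–6% for every method: the issue is power, not false positives.

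**6. Grouping.** Sections 2.1 and 2.6 and the opening of 2.10.2 all describe two groups; only this sentence refers to dose groups. The introduction mentions a separate study of "efficacy and safety of HAD-B1 for dose-finding in EGFR-positive NSCLC subjects who need afatinib therapy is currently in progress", which may be where the wording came from, though that is inference.

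**The case against.** A reader might infer that the plan commits to absolute change in means, and that a real marker effect would therefore probably be missed. The documents do not support that:

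- The text says reduction without a scale. Percent or log change is not excluded, and a journal article commonly leaves scale and transformation to the full protocol or analysis plan. Silence on scale is not in itself an error.
- The sentence also lists median, minimum and maximum and offers a Wilcoxon test, so the plan is not tied to means.
- Skew and proportional effects are assumptions. Depending on them, t-test power on absolute change in the second model runs from about 94% down to about 8%. The simulations generate log-normal data, which favours a log analysis by construction.
- The gain from adjustment is also assumption-dependent. If log change is unrelated to baseline, as in the second model, ANCOVA on log change has no advantage over the unadjusted log test.
- The grouping label misleads few readers, because the section opens by naming treatment and control.

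All of this limits the size of the point. What stands is what the article does fix: an unadjusted between-group test where baseline is at hand, and a grouping that the design lacks. The Wilcoxon option is a weak defence as written, because the named test appears to be the signed rank test, a paired procedure unsuited to independent arms. The rank-sum figures above are for a test that the article does not name.

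**Conclusion.** The point holds as a modest, low-cost improvement to secondary analyses, together with one definite wording error.

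- **Certain:** the dose-group label does not fit a trial with two randomised arms and one HAD-B1 dose.
- **Well supported:** the planned comparison ignores baseline as a covariate. At 64 per arm, ratio 0.60 and ρ = 0.6, adjustment adds about 5 points of power at log-SD 1.0 and 9 to 10 points at log-SD 1.5. At ρ = 0.8 it adds 3 points or fewer.
- **Conditional:** if the reduction is analysed as absolute change and the markers are right-skewed, the loss against a log analysis can be large, by an amount set by the assumed skew and control-arm decline. For tumour size it may be small if baseline spread is modest and change is not very variable (94% against 100% at log-SD 0.4 with SD of log change 0.5).

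The documents do not show that the analysis is on an absolute scale, that extreme baselines dominate it, or that an effect would be missed.

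**What to change.** In section 2.10.2:

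1. Compare the two randomised arms by ANCOVA with the baseline value as covariate.
2. For CEA and NSE, analyse the log ratio to baseline with log baseline as covariate, and report the geometric mean ratio with 95% CI.
3. For tumour size, analyse percent change in the RECIST 1.1 sum of diameters, with the baseline sum as covariate.
4. Replace the dose-group label with treatment group.
5. If a rank test is kept as a supportive analysis, name the rank-sum test and apply it to the relative change.

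A supportive analysis in patients whose marker was above the laboratory's upper limit of normal at baseline is optional.

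The cost is analysis wording only: no added patients, visits or samples. As the trial is open-label, the change should be made before outcome data are examined. If the full protocol or analysis plan already fixes the scale and the adjustment, aligning the published wording is enough.

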#### Exploratory outcome variables

2.10.3

We will explore whether treatment reaction and prognosis vary according to cold-heat pattern predisposition. For categorical variables, the frequency and the percentage for each administration group will be presented, and the statistical significance for the differences between groups will be tested by using the Chi-Squared test or Fisher exact test. For continuous variables, descriptive statistics (number of subjects, mean, standard deviation, median value, minimum, and maximum values) for each group will be presented, and the statistical significance of differences between groups will be tested by using the two-sample *t* test or Wilcoxon signed rank test.

### Safety assessment

2.11

The number of subjects who will present with adverse events, adverse drug reactions, serious adverse events, and events of special interests, as well as the ratio of those subjects to the total number in the group at baseline, will be recorded. The significance of differences between groups will be tested by using the Chi-Squared test or Fisher exact test. The amount of change at 16 weeks of treatment compared to the baseline for laboratory tests, vital signs, and electrocardiogram (ECG) results will be compared between groups. For continuous variables, descriptive statistics (number of subjects, mean, standard deviation, median value, minimum and maximum values) for the amount of change at 16 weeks of treatment compared to the baseline will be presented, and the statistical significance of differences between groups will be tested by using the paired *t* test or the Wilcoxon signed rank test. While for categorical variables among laboratory tests and ECG results, their frequency will be presented using a contingency table for normal/abnormal changes at 16 weeks of treatment compared to the baseline, and the significance of changes between groups will be tested by using the *t* test, Chi-Squared test, or Fisher exact test.

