**Table 1 T1:** Components of HAD-B1.

Scientific name	Plant parts used	Representative component	Amount (mg)
Panax Notoginseng (Burk) F.H. Chen	Root	Notoginsenoside R1	839
Cordyceps militaris	Fruit and corpus	Cordycepin	640
Panax ginseng C.A. Meyer	Root	Ginsenoside Rg1 and Rb1	640
Boswellia carterii BIRDWOOD	Mastic	a-boswellic acid, b-boswellic acid	400

The aim of this study is to use a multicenter, randomized, controlled trial to explore the efficacy and safety of combination therapy with afatinib plus HAD-B1 in the treatment of patients with locally advanced or metastatic NSCLC who have an activating EGFR mutation. Moreover a cold-heat pattern identification questionnaire (CHPIQ) of NSCLC patients will be conducted to explore whether the prognosis varies according to cold-heat pattern in Korean medicine.

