### Safety assessments

2.7

During the study period, subjects will be continuously monitored for frequency, severity, and aspect of events of special interests (ESIs). ESIs include paronychia, loss of appetite, diarrhea, stomatitis, cheilitis, rash, acne dermatitis, interstitial lung disease, and severe hepatopathy. The overall safety profile will be evaluated by using safety indicators such as the numbers of abnormal cases and adverse drug reactions, the frequency of significant abnormalities, as well as severities and aspects of abnormalities, physical examination findings, abnormal vital signs, clinical laboratory findings, and clinically significant changes in the ECOG PS scores. The treatment discontinuation rate and reason will be recorded.

In this clinical trial, the “Data and Safety Monitoring Board (DSMB)” will be operated as a safety protection measure for the test subjects. The board will meet every 6 months after the commencement of the study to evaluate the overall safety of clinical trials.

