### Sample size calculation

2.9

According to the paper, the Afatinib group’s starting dose maintenance rate is assumed to be 57.6 percent, while the Afatinib + HAD B1 group’s starting dose maintenance rate is assumed to be 80.0 percent. Furthermore, it is assumed that all patients will be recruited and monitored for at least 16 weeks. As a result, each group has 64 test subjects. With a 10% dropout rate, 71 people will be recruited for a total of 142 people.^[14]^

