In light of the above, this prospective, multicenter, randomized, controlled trial will verify the efficacy and safety of a combination therapy of afatinib plus HAD-B1 in treating patients with locally advanced or metastatic NSCLC. At the same time, this trial may provide clinical evidence supporting integrative medicine and may propose synergistic effects of treating such patients with this combination therapy.

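### The article promises to verify the safety of adding HAD-B1, but the only between-arm inference it states for adverse events is a difference test, and at 71 per arm a non-significant result cannot support that promise

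*Protocol article*

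**What the plan says.** All references are to the protocol article.

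- **Strength of the safety claim.** The closing paragraph of the Discussion says the trial "will verify the efficacy and safety of a combination therapy of afatinib plus HAD-B1". The aim at the end of the Introduction is weaker: "to explore the efficacy and safety of combination therapy with afatinib plus HAD-B1". Comparing safety is also part of the title and of section 2.1.
- **Adverse-event analysis (2.11).** Numbers of subjects with events are reported, "as well as the ratio of those subjects to the total number in the group at baseline, will be recorded". Then: "The significance of differences between groups will be tested by using the Chi-Squared test or Fisher exact test". No risk difference, confidence interval or margin is attached.
- **Events in view (2.7).** "ESIs include paronychia, loss of appetite, diarrhea, stomatitis, cheilitis, rash, acne dermatitis, interstitial lung disease, and severe hepatopathy".
- **Other safety review (2.7).** Severity, laboratory findings and discontinuations with reasons are recorded, and there is a monitoring board: "The board will meet every 6 months after the commencement of the study to evaluate the overall safety of clinical trials".
- **Size (2.9).** The calculation uses only starting dose maintenance. The control "starting dose maintenance rate is assumed to be 57.6 percent", against 80.0% with the combination. It arrives at 64 per group. "With a 10% dropout rate, 71 people will be recruited for a total of 142 people".

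**The concern.** HAD-B1 is given on top of afatinib. Unless events fall significantly in the combination arm, a difference test can end in only two ways: harm is detected, or the result is not significant. The second outcome does not show that the combination is acceptably safe. It shows only that the data did not separate the arms, and in a trial sized for a 22.4-point difference in another endpoint that can easily happen when harm is present. The verb in the Discussion therefore promises more than the stated method can deliver, and it is also stronger than the Introduction's own aim. At stake is the safety statement in the final report. A p-value above 0.05 hides how much excess risk is still compatible with the data, whereas an interval from the same counts would show it.

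**Working it through.** **1. The plan's own figure.** Section 2.9 states neither alpha nor power. Assuming two-sided 5% and 80%, with unpooled variance:

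n = (1.960 + 0.842)² × [0.576×0.424 + 0.800×0.200] / 0.224² = 63.2, rounded up to 64 per group, as stated.

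64 × 1.10 = 70.4, rounded up to 71, also as stated. The size is thus accounted for by dose maintenance alone, and no safety quantity enters it.

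**2. Power of the stated test for adverse events.** The article gives no control event rate and no size of relevant harm, so the rates below are assumptions. The method is to enumerate every pair of binomial counts with n = 71 per arm and sum the probability of those with two-sided p < 0.05, once for Fisher's exact test and once for the uncorrected chi-square test. The denominator of 71 assumes that everyone randomised is counted.

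| Afatinib alone vs combination | Fisher power | Chi-square power | Missed |
|---|---|---|---|
| 2% vs 6% | 8.5% | 21% | 79–91% |
| 10% vs 20% | 31% | 39% | 61–69% |
| 30% vs 45% | 38% | 46% | 54–62% |
| 5% vs 15% | 41% | 53% | 47–59% |
| 15% vs 30% | 50% | 59% | 41–50% |
| 30% vs 50% | 62% | 69% | 31–38% |
| 20% vs 40% | 69% | 76% | 24–31% |
| 10% vs 30% | 82% | 87% | 13–18% |
| 25% vs 50% | 83% | 88% | 12–17% |

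At 64 per arm, power is lower by about 2 to 6 points.

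**3. What an interval would show.** The Newcombe interval for the difference d = p₂ − p₁ uses the Wilson limits (l, u) of each arm: lower = d − √[(p₂−l₂)² + (u₁−p₁)²], upper = d + √[(u₂−p₂)² + (p₁−l₁)²].

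- 4/71 with the combination versus 1/71 with afatinib alone: Fisher p = 0.37. p₂ = 5.63% (Wilson 2.21 to 13.61), p₁ = 1.41% (0.25 to 7.56), d = 4.23 points. Lower = 4.23 − √(3.42² + 6.15²) = −2.8. Upper = 4.23 + √(7.98² + 1.16²) = +12.3 points.
- 2/71 versus 2/71: p = 1.0. Each arm is 2.82% (0.78 to 9.70), so the limits are ±√(6.88² + 2.04²) = ±7.2 points.

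For commoner events with equal observed rates, the approximate 95% half-width 1.96√[2p(1−p)/71] is 7 points at p = 5%, 10 at 10%, 13 at 20%, 15 at 30% and 16 at 50%.

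**4. Would a formal margin be feasible?** To exclude a 10-point excess with one-sided 2.5% alpha, 80% power and equal true rates, n = (1.960 + 0.842)² × 2p(1−p) / 0.10². This gives 142 per arm at p = 10%, 252 at 20%, 330 at 30% and 393 at 50%. With 71 per arm it is not feasible at these rates.

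**The case against.** The strongest reply is that the article contains no rule equating a non-significant test with safety. A reader might infer such a rule by joining the Discussion's verb to section 2.11, but the text does not state it. *Verify* appears once, in a closing sentence covering efficacy and safety together, and the formal aim says only *explore*. This stands, and it limits the point to a mismatch between a stated claim and a stated method.

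A reader might also infer that the test would miss relevant harm in most trials, or would usually miss a doubling or tripling of toxicity. The figures do not support that in general. The doublings from 20% to 40% and from 25% to 50% have power of 69–76% and 83–88%, and the tripling from 10% to 30% has 82–87%. For 5% versus 15% and 15% versus 30%, detection is roughly an even chance.

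Other parts stand in part. Intervals may appear in a fuller protocol or analysis plan that is not shown, and anyone can derive them from the reported counts. Their absence from an article would not be a finding by itself. The point is that the article does name an inferential method and pairs it with a conclusion that the method cannot reach. Severity review, recorded discontinuations and the monitoring board also mean that safety does not rest on this test alone, but section 2.7 gives no between-arm estimate of excess risk. Finally, the trial is sized for better dose maintenance, which bears on tolerability, and a difference test suits a hypothesis of fewer events. It does not help if the event rates turn out not to differ significantly.

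**Conclusion.** The point holds in a limited form. The article promises verification of safety in one place and exploration in another. The only between-arm inference it states for adverse events is a significance test, in a trial sized on dose maintenance alone. A non-significant result from that test cannot carry a safety conclusion. Under the assumed rates, moderate increases and increases in rare events are often missed: 61–69% of the time for 10% versus 20%, and 79–91% for 2% versus 6%. The latter would apply to interstitial lung disease or severe hepatopathy if these are rare in this population, which is itself an assumption. Large increases in common events are usually detected. The size of the problem depends wholly on event rates that the article does not give, but the logical mismatch does not. The primary analysis is unaffected. The change should be made because it costs almost nothing and concerns one of the trial's headline claims.

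**What to change.** 1. In section 2.11, for adverse events, adverse drug reactions, serious adverse events and each event of special interest, make the risk difference (combination minus afatinib alone) with a two-sided 95% Newcombe or exact confidence interval the main between-arm summary.
2. Add a sentence that a non-significant p-value is not taken as evidence of safety.
3. In the closing paragraph of the Discussion, replace the promise to verify safety with one to *describe the safety, with 95% confidence limits on excess risk*. This also brings it into line with the Introduction.

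No formal margin should be added, since the sample size could not support one of 10 points at event rates of 10% or more. The interval is therefore a description of what remains possible and not a pass/fail rule.

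The cost is a few lines of text and code, with no extra patients or data. The downside is that intervals for rare events will be wide relative to the event rates, and the safety statement will read less favourably.
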